#### Procedure of the trial

Routine preparations are conducted before upper gastrointestinal endoscopy (generally fasting for at least 6 h preoperatively and no drinking water for at least 2 h). Before inducing sedation for upper gastrointestinal endoscopy, venous access will be established. During the procedure, peripheral oxygen saturation (SpO_2_), heart rate, continuous right upper limb noninvasive blood pressure, and Modified Observer’s Assessment of Alertness/Sedation (MOAA/S) score will be monitored. Specific monitoring indicators are presented in Table 2. Perioperative respiratory-related adverse events and participants’ treatment methods are shown in Table 3, and adverse events of anesthesia and sedation are shown in Table 4.

**Table 2 Tab2:** The specific monitoring indicators

Monitoring indicators	Stage	Monitoring frequency
SpO_2_, heart rate, blood pressure, MOAA/S score	Before beginning sedation induction	After taking lidocaine hydrochloride mucilage and entering the room, the patient is placed in the left decubitus position on the examination bed, and indicators are recorded:
	Sedation induction started when fully awake	(1) The initial dose of remimazolam or propofol is intravenously administered (this time will be recorded as 0 min) (2) Within 1 min after the initial intravenous dose (3) When the upper gastrointestinal endoscope is successfully inserted (4) After successfully inserting the upper gastrointestinal endoscope, every 3 min until the end of upper gastrointestinal endoscopy (5) At the end of upper gastrointestinal endoscopy (6) When the patient is fully alert (MOAA/S score of 5 points for three consecutive times; for an MOAA/S score of 5, it should reach 5 the next two times).

**Table 3 Tab3:** Perioperative respiratory-related adverse events and treatment records

SpO_2_ before the procedure (no oxygen)		Lowest SpO_2_ during the procedure		Is SpO_2_ <90% during the procedure?	Yes □ No□
Duration of SpO_2_ <90%		Did oxygen flow increase during the procedure?	Yes □ No □	Is the patient's mandible lifted?	Yes □ No□
Is mask ventilation required?	Yes□ No□			Is endotracheal intubation performed?	Yes □ No □

Treatment of respiratory-related adverse events: When SpO_2_ is <95%, the participant will be lifted to the mandible. If SpO_2_ is <90%, the oxygen flow of the nasal catheter will be increased to 6L/min. If SpO_2_ is still <90%, the procedure will be stopped, the upper gastrointestinal endoscope will be pulled out, and positive pressure ventilation will be performed using a mask. If SpO_2_ cannot be corrected, laryngeal mask airway or tracheal intubation will be performed to control breathing

**Table 4 Tab4:** Adverse events of anesthesia and sedation

Step 1: Was there one or more adverse events associated with this sedation encounter?				
No, this form is now complete.	Yes, fill out remainder of form below.			
Step 2: Please DESCRIBE the adverse events(s). Check all that apply.				
Minimal risk descriptors	Minor risk descriptors		Sentinel risk descriptors	
Vomiting/Retching	Oxygen desaturation (75–90%) for <60s		Oxygen desaturation, severe (<75% at any time) or prolonged (<90% for >60s)	Other, specify below
Subclinical respiratory depression^a^	Apnea, not prolonged		Apnea, prolonged (>60 s)	
Muscle rigidity, myoclonus	Airway obstruction		Cardiovascular collapse/shock^g^	
Hypersalivation	Failed sedation^e^		Cardiac arrest/absent pulse	
Paradoxical response^b^	Allergic reaction without anaphylaxis			
Recovery agitation^c^	Bradycardia^f^			
Prolonged recovery^d^	Tachycardia^f^			
	Hypotension^f^			
	Hypertension^f^			
	Seizure			
Step 3: Please note the INTERVENTIONS performed to treat the adverse events(s). Check all that apply.				
Minimal risk	Minor risk	Moderate risk	Sentinel intervention	
No intervention performed	Airway repositioning	Bag valve mask-assisted ventilation	Chest compressions	Other, specify below
Administration of:	Tactile stimulation	Laryngeal mask airway	Tracheal intubation	
Additional sedative(s)	or the administration of:	Oral/nasal airway	or the administration of:	
Antiemetic	Supplemental oxygen, new or increased	Continuous positive airway pressure (CPAP)	Neuromuscular block	
Antihistamine	Antisialogogue	or the administration of:	Pressor/epinephrine	
		Reversal agents	Atropine to treat bradycardia	
		Rapid i.v. fluids		
		Anticonvulsant i.v.		
Step 4: Please note the OUTCOME of the adverse events(s). Check all that apply.				
Minimal risk outcome	Moderate risk outcome		Sentinel outcome	
No adverse outcome	Unplanned hospitalization or escalation of care^h^		Death	Other, specify below
			Permanent neurological deficit	
			Pulmonary aspiration syndrome^i^	
Step 5: Assign a SEVERITY rating to the adverse event(s) associated with this sedation encounter.				
If there are any options checked in the Sentinel columns above, then this is a Sentinel^j^ adverse event.				
If the most serious option(s) checked above are Moderate risk, then this is a Moderate^k^ risk adverse event.				
If the most serious option(s) checked above are Minor risk, then this is a Minor^l^ risk adverse event.				
If the most serious option(s) checked above are Minimal risk, then this is a Minimal^m^ risk adverse event.				

Additional details (including “other” entries):

Footnotes:

^a^“Subclinical respiratory depression” is defined as capnographic abnormalities suggesting respiratory depression that do not manifest clinically

^b^“Paradoxical response” is defined as unanticipated restlessness or agitation in response to sedatives

^c^“Recovery agitation” is defined as abnormal patient affect or behaviors during the recovery phase that can include crying, agitation, delirium, dysphoria, hallucinations, or nightmares

^d^“Prolonged recovery” is defined as failure to return to baseline clinical status within 2 h

^e^“Failed sedation” is defined as inability to attain suitable conditions to humanely perform the procedure

^f^Alteration in vital signs (bradycardia, tachycardia, hypotension, hypertension) is defined as a change of >25% from baseline.

^g^“Cardiovascular collapse/shock” is defined as clinical evidence of inadequate perfusion

^h^Examples of “escalation of care” include transfer from ward to intensive care, and prolonged hospitalization

^i^“Pulmonary aspiration syndrome” is defined as known or suspected inhalation of foreign material such as gastric contents into the respiratory tract associated with new or worsening respiratory signs

^j^“Sentinel” adverse events are those critical enough to represent real or serious imminent risk of serious and major patient injury. Once recognized, they warrant immediate and aggressive rescue interventions. Once clinically concluded, they warrant immediate reporting within sedation care systems, and the highest level of peer scrutiny for continuous quality improvement

^k^“Moderate” adverse events are those that, while not sentinel, are serious enough to quickly endanger the patient if not promptly managed. Once clinically concluded, they warrant timely reporting within sedation care systems, and periodic peer scrutiny for continuous quality improvement

^l^“Minor” adverse events are those encountered periodically in most sedation settings and that pose little threat given appropriate sedationist skills and monitoring.

^m^“Minimal” adverse events are those that alone present no danger of permanent harm to the patient

All participants will receive 10 g of 2% lidocaine hydrochloride mucilage. They will be administered supplemental oxygen (3–4 L/min) before injecting sufentanil until the participants are fully alert after the procedure. Approximately 1 min after administering 5 μg of sufentanil, remimazolam tosylate 0.15 mg/kg, remimazolam tosylate 0.2 mg/kg, or propofol 1.5 mg/kg will be used to induce sedation. If the MOAA/S score is ≤2, upper gastrointestinal endoscope intubation will be initiated. If the MOAA/S score is still >2 after two min or if the upper gastrointestinal endoscopy attempt fails because the participant is writhing or nauseating, the experimental group will be given remimazolam tosylate (0.05 mg/kg) and the control group will be given propofol (0.5 mg/kg). The administration time is 10 s, and the interval between each supplementation dose is at least 1 min. After the endoscope intubation, to maintain a certain degree of sedation (MOAA/S score, ≤2), additional remimazolam tosylate or propofol will be administered as necessary. If two doses (after the initial dose) within any 5-min window are not sufficient to obtain or maintain adequate sedation, the case will be designated a treatment failure and rescue sedative medication (propofol) will be administered to obtain or maintain adequate sedation to complete upper gastrointestinal endoscopy.

Participants may have perioperative respiratory-related adverse events during upper gastrointestinal endoscopy. If the SpO_2_ is <95%, we will lift the patient’s mandible. If it is <90%, we will increase the oxygen flow of the nasal catheter to 6 L/min. If the SpO_2_ is still <90%, we will suspend the procedure, pull out the upper gastrointestinal endoscope, and perform positive pressure ventilation with a mask. If it still cannot be corrected, laryngeal mask airway or tracheal intubation will be performed to control breathing. During the procedure, participants with hypotension or bradycardia will be administered ephedrine or atropine, as appropriate.

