### Aims and objectives

Compared with propofol, the safety and efficacy of remimazolam tosylate during upper gastrointestinal endoscopy are verified based on the completion of upper gastrointestinal endoscopy, vital signs of participants, and satisfaction of endoscopists and patients.

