#### Allocation masking

This study follows a single-blinded method. All participants are blinded to the assignment of the trial (the injection site will be shielded) and will be randomly assigned to any of the three groups.

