##### Additional analyses

Subgroup analysis: Subgroup analysis via an interaction by gender, age (18–24, 25–44, and 45–60 years), and BMI (<23 and ≥23 kg/m^2^) will be used to analyze the primary and secondary outcomes among subgroups.Safety analysis: General safety evaluations will be based on the incidence and type of adverse events. Safety variables will be tabulated and presented for all participants in the safety set. Adverse events will be coded using the World SIVA adverse sedation event reporting tool. The number (%) of participants with any adverse events will be summarized.

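### Four vital-sign events with a numeric definition are counted from form ticks, although the readings that decide them are recorded for every participant and could supply the count

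*Protocol article*

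**What the plan says.** All references are to the protocol article.

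- **Aim.** Under Aims and objectives, safety and efficacy "are verified based on the completion of upper gastrointestinal endoscopy, vital signs of participants, and satisfaction of endoscopists and patients".
- **Recording tool.** Outcome measures states that adverse events during the procedure are recorded with the World SIVA tool. This is Table 4 under Procedure of the trial.
- **Opening question.** Step 1 of Table 4 asks whether there was any adverse event. The negative answer reads "No, this form is now complete". A positive answer leads to "Step 2: Please DESCRIBE the adverse events(s). Check all that apply", where hypotension, hypertension, bradycardia and tachycardia are boxes.
- **Definition.** Footnote f to Table 4: "Alteration in vital signs (bradycardia, tachycardia, hypotension, hypertension) is defined as a change of >25% from baseline".
- **Readings.** Table 2 lists "SpO_2_, heart rate, blood pressure, MOAA/S score", taken before induction, at the initial dose, within 1 min of it, at insertion, then "After successfully inserting the upper gastrointestinal endoscope, every 3 min until the end of upper gastrointestinal endoscopy", at the end of the procedure and at full alertness.
- **Analysis.** Statistical analysis plan assigns the chi-square test to the incidence of adverse events, two-sided at 0.05. Additional analyses says "General safety evaluations will be based on the incidence and type of adverse events", coded with the same SIVA tool.
- **Blinding.** Allocation masking: "All participants are blinded to the assignment of the trial". No other role is named as blinded.

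**The concern.** The four events follow from arithmetic on recorded numbers, so they can be counted in the same way in every arm. The stated count instead needs someone to answer Step 1 positively and then tick the right box. Two things can go wrong.

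- **Equal under-recording.** If events are missed equally often in all arms, a true difference shrinks and power is lost.
- **Arm-dependent recording.** If events are looked for harder in one arm, a difference can appear where none exists.

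The second matters here because Background and Discussion both present less hypotension than with propofol as an expected advantage of remimazolam. In a single-blind trial, that expectation can influence a judgement-based entry. The section on adverse event reporting and harm adds that drug-related events are collected in a non-systematic way, which does not reassure.

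**Working it through.** The plan states no figure on this point, so there is none to reproduce. The check has two parts.

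**1. The sections side by side**

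| Step | Where | Content |
|---|---|---|
| Definition | Table 4, footnote f | more than 25% change from baseline |
| Deciding data | Table 2 | blood pressure and heart rate before induction and at set times |
| Stated record | Outcome measures; Table 4 | SIVA form, box ticked after a positive Step 1 |
| Stated coding and test | Additional analyses; Statistical analysis plan | SIVA tool; chi-square on incidence |

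No section joins the second row to the third or fourth.

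**2. How large the effect could be (illustration)**

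Inputs from the article: 600 per arm (Sample size); two-sided 0.05 (Statistical analysis plan). Assumptions, because the article gives no figures: the true event rates, the share of events ticked, and a pairwise comparison of one remimazolam arm with propofol with all 600 per arm contributing.

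The recorded rate is the true rate times the share ticked; call the two recorded rates a and b, with mean m. Then

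P(significant in the direction of the larger rate) = Φ{ [√n·|a−b| − 1.96·√(2m(1−m))] / √(a(1−a)+b(1−b)) }.

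The other tail is added to obtain the total, which is compared with the nominal 5%.

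*No true difference, unequal ticking.* Take a true 20% in both arms (120 events each), with 90% and 75% ticked.
- Recorded: a = 0.18 (108 events), b = 0.15 (90 events), m = 0.165.
- √600 × 0.03 = 0.735; 1.96 × √(2 × 0.165 × 0.835) = 1.96 × 0.5249 = 1.029; denominator √(0.1476 + 0.1275) = 0.5245.
- (0.735 − 1.029)/0.5245 = −0.56, and Φ(−0.56) = 0.29. The other tail adds less than 0.001.

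Total chance of a significant result, same formula:

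| True rate, both arms | 90% vs 80% ticked | 90% vs 70% ticked |
|---|---|---|
| 5% | 7% | 14% |
| 10% | 10% | 25% |
| 20% | 15% | 47% |
| 30% | 22% | 68% |

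In the direction of the more fully ticked arm alone, the first two entries of the middle column are 6% and 9%, against a nominal 2.5%. The other entries do not change at this rounding.

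*True difference, equal ticking.* Take a true 30% vs 20%.
- All ticked: √600 × 0.10 = 2.449; 1.96 × √(2 × 0.25 × 0.75) = 1.200; denominator √(0.21 + 0.16) = 0.608; Φ(2.05) = 0.98.
- 70% ticked (21% vs 14%): 0.89. 60% ticked (18% vs 12%): 0.83. 50% ticked (15% vs 10%): 0.75.
- For a smaller true difference, 20% vs 13%: 0.91 with full ticking, 0.76 at 70%, 0.60 at 50%.

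Equal under-recording therefore costs power but creates no false difference. Unequal recording does create one, and the effect grows with the event rate.

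**The case against.** The case on the other side has real substance.

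- **Who ticks, and when, is not stated.** Allocation-aware staff are a reasonable inference from the single-blind design, not a stated fact. A reader might picture staff working out percentage changes in the middle of sedation. The form does not support that: it asks for outcome, severity and recovery that may be prolonged to 2 h, so it can be finished only afterwards, when the Table 2 values are on record. Footnote f gives one rule for all arms, and nothing says it is applied without looking at those values. This stands, and it limits the point to a missing safeguard.
- **Ticks are not the only use of vital signs.** A reader might infer that blood pressure and heart rate reach the analysis only as ticks. Additional analyses also says safety variables will be tabulated for the safety set, and these readings may be among them. However, tabulation does not determine how the tested events are counted.
- **Desaturation.** A reader might extend the point to hypoxia. The article does not support that: Table 3 records lowest SpO2 and time below 90% independently of Step 1, hypoxia has its own numeric definition among the secondary outcomes, and no section says it is counted from Table 4. What remains is that its source form is not named.
- **Table 2 is intermittent.** Readings are 3 min apart after insertion while monitoring is described as continuous, so a tick can catch a brief change that Table 2 misses. Nor is Table 2 said to be recorded by blinded staff, and treatment of hypotension or bradycardia alters later readings. Derivation removes the judgement about ticking; it does not remove these limits.
- **An unseen document may hold the rule.** The full protocol or analysis plan could link the ticks to Table 2. The point survives because the article does more than stay silent: it names the SIVA tool as both the recording and the coding source.

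**Conclusion.** The point holds for hypotension, hypertension, bradycardia and tachycardia. The article counts these numerically defined events from ticks behind a single yes/no question, in a trial where only participants are named as blinded, and does not link the count to readings it already collects. A uniform derivation is available and less open to bias.

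The size is conditional. With 10 to 20 percentage points between the shares ticked in the two arms and no true difference, the chance of a spurious finding runs from about 7% to 14% at a true rate of 5%, and from 15% to 47% at 20%. None of these rates comes from the article. They show what could happen, and it would be wrong to read them as evidence that recording will differ by arm. The primary outcome is not affected. For hypoxia, no error is shown; naming the source would be a clarification. This is a correction worth making before analysis, not a flaw that undermines the trial.

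**What to change.** 1. In Statistical analysis plan and Additional analyses, state that the four events are derived by program from the Table 2 values for every dosed participant, whatever was answered at Step 1. Use the protocol's own rule of more than 25% change, measured against the pre-induction reading. The sponsor should also name the blood-pressure component, which footnote f leaves open.
2. Report the ticked events as a supplement, because brief changes between recording times may appear only there. Keep the SIVA form for events without a numeric source, and for interventions, outcomes and severity.
3. Name Table 3 (lowest SpO2 and duration) as the source for the hypoxia outcome.
4. Optionally, compare blood pressure and heart rate as continuous measures, adjusted for baseline, at time points common to all participants, such as within 1 min of the initial dose and at insertion. The largest fall is a poor choice: the number of readings grows with procedure length, so it depends on how often each participant was measured.

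The cost is some wording and a short derivation program, with no new data or visits. The downside is that brief events between readings appear only in the supplement.

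### Table 4 turns Minor hypotension or bradycardia into a Sentinel event once a pressor or atropine is given, so a Sentinel total can be driven by open-label treatment decisions

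*Protocol article*

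**What the plan says.** Four places in the protocol article bear on this point.

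- **Table 4, Step 2 and footnote f.** Hypotension and bradycardia sit in the Minor column. The threshold is given in the footnote: "Alteration in vital signs (bradycardia, tachycardia, hypotension, hypertension) is defined as a change of >25% from baseline".
- **Table 4, Step 3.** The Sentinel intervention column contains "Pressor/epinephrine" and "Atropine to treat bradycardia".
- **Table 4, Step 5 and footnote j.** The rule begins "If there are any options checked in the Sentinel columns above" and assigns the Sentinel grade. Footnote j keeps that grade for events that put the patient in real or impending danger of grave harm. Footnote l describes Minor events as posing little threat when skill and monitoring are adequate.
- **Procedure of the trial, closing text.** During the procedure, "participants with hypotension or bradycardia will be administered ephedrine or atropine, as appropriate". No numerical trigger is attached.

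Allocation masking states blinding for participants only. Outcome measures and Additional analyses say that adverse events are recorded and coded with this reporting tool.

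**The concern.** A grade that is meant to describe what happened to the patient here depends partly on what the staff chose to give. A fall in pressure of more than 25% that resolves untreated is Minor. The same fall treated with ephedrine, as the procedure text provides, passes over Moderate and becomes Sentinel. The people who give the drug are not stated to be blinded.

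Safety against propofol is one of the trial's aims, and the Abstract anticipates a safer experience than with propofol. If Sentinel totals are set side by side by arm, a difference in readiness to treat would look like a difference in critical events. The documents do not say which arm would be treated more readily, so the direction of any distortion is open.

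**Working it through.** **Classification trace.** Take a participant whose only event is hypotension or bradycardia as defined in footnote f.

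| | Not treated with a drug | Ephedrine or atropine given |
|---|---|---|
| Step 2 descriptor | Minor | Minor |
| Step 3 intervention | no Sentinel box | Sentinel box |
| Step 4 outcome | no adverse outcome | no adverse outcome |
| Step 5 grade | Minor | Sentinel |

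Atropine is named on the form. Ephedrine is not, but it is a pressor and so falls under that box.

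**Size.** The plan states no figure to reproduce. The inputs are:

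- *n* = 600 per arm, from Sample size.
- *h*, the proportion with hypotension or bradycardia: not given, assumed.
- *t*, the proportion of those who get ephedrine or atropine: not given, assumed.
- *s*, the proportion Sentinel by any other route: not given, assumed, and taken as independent of *h* and *t*.

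The Sentinel proportion in an arm is *p* = 1 − (1 − *ht*)(1 − *s*). Let *h* and *s* be the same in two arms and only *t* differ:

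| *h* | *s* | *t* (arm A, arm B) | *p* in A | *p* in B | Expected number of 600 | Chance of p<0.05 |
|---|---|---|---|---|---|---|
| 20% | 1% | 25%, 50% | 1 − 0.95 × 0.99 = 5.95% | 1 − 0.90 × 0.99 = 10.9% | 35.7 vs 65.4 | about 87% |
| 10% | 1% | 25%, 50% | 1 − 0.975 × 0.99 = 3.475% | 1 − 0.95 × 0.99 = 5.95% | 20.9 vs 35.7 | about 53% |
| 5% | 3% | 10%, 20% | 1 − 0.995 × 0.97 = 3.485% | 1 − 0.99 × 0.97 = 3.97% | 20.9 vs 23.8 | about 6% |

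The last column is the normal approximation for two proportions, two-sided 5%, counting significance in the direction of the difference:

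*z* = {|*p*B − *p*A| − 1.96 √[2*p̄*(1 − *p̄*)/*n*]} / √{[*p*A(1 − *p*A) + *p*B(1 − *p*B)]/*n*}.

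Row 1: *p̄* = 0.08425, *z* = (0.0495 − 0.0314)/0.0160 = 1.13, probability 0.87. Row 3: *p̄* = 0.0373, *z* = (0.00485 − 0.0214)/0.0109 = −1.52, probability 0.06.

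**Share of Sentinel participants graded so only through ephedrine or atropine.** This is *ht*(1 − *s*)/*p*.

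- *h* = 2%, *t* = 10%, *s* = 5%: 0.0019/0.0519 = about 4%.
- *h* = 10%, *t* = 25%, *s* = 3%: 0.02425/0.05425 = about 45%.
- *h* = 10%, *t* = 25%, *s* = 1%: 0.02475/0.03475 = about 71%.
- *h* = 30%, *t* = 90%, *s* = 0.5%: 0.26865/0.27365 = about 98%.

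**The case against.** The strongest reply is that no named analysis is affected. Additional analyses plans the incidence and type of adverse events and the number of participants with any event. The Statistical analysis plan section applies the chi-square test to the incidence of adverse events. Neither mentions a Sentinel count. Hypotension and bradycardia reported by type do not change with the Step 5 grade. This stands, and it limits the point. It does not remove it, because Step 5 requires a severity grade for every encounter with an event, so the totals will exist and can be reported by arm.

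A second reply is that the form is an adopted tool, built to grade by the worst descriptor, intervention or outcome, and that needing a drug is itself a sign of severity. That is fair: the form contains no error of its own. The difficulty comes from joining it to open-label treatment with no stated trigger, which leaves a true difference in severity and a difference in prescribing indistinguishable in the total.

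Four stronger readings are tempting, and the documents do not support them.

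- *That Sentinel counts will mostly reflect prescribing.* Sentinel is also reached through severe or prolonged desaturation, prolonged apnea, shock, arrest, intubation and other routes. With no rates given, the drug-only share runs from about 4% to about 98%.
- *That true critical events would be hidden.* Steps 2 to 4 record them in separate boxes, and Table 3 separately records lowest saturation, its duration below 90%, mask ventilation and intubation.
- *That any excess of Sentinel events under propofol would be a prescribing artefact.* The Background expects less hypotension with remimazolam. If incidence differs and the same proportion is treated, the excess follows a real difference in incidence.
- *That a jaw lift at a saturation of 90–94% creates a Minor event in the same way.* Step 1 closes the form when there is no adverse event, and Step 3 covers only interventions given to treat one.

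**Conclusion.** The point holds in limited form and is a cheap improvement. Followed literally, Table 4 and the procedure text let the same recovered event be graded Minor or Sentinel according to an open-label decision to give ephedrine or atropine, which sits badly with footnote j. Any between-arm Sentinel total can be moved by this. Under assumed rates that are equal in both arms, the shift ranges from negligible (3.5% versus 4.0%) to large (5.95% versus 10.9%). These figures rest on assumed event rates, assumed treatment proportions and independence of the other Sentinel routes. They illustrate the mechanism and do not forecast this trial. The primary outcome and the incidence of hypotension and bradycardia by type are untouched.

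**What to change.** Keep the form and its standard severity grade. Pre-specify that Sentinel events are also tabulated by trigger: Step 2 descriptor, Step 3 intervention, Step 4 outcome. Put events that are Sentinel only because ephedrine or atropine was given on their own line, and state that this line is not to be read as a count of critical events.

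The closing text of Procedure of the trial and Table 4 should be reconciled so that readers and sites can see how a treated Minor event is graded. This should not tell sites to override Step 5, and it needs no treatment threshold; the clinical rule is for the investigators.

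Steps 2 to 4 already collect the data. The cost is a paragraph of analysis wording and one extra safety table beside the tool's standard total.

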
Remimazolam tosylate is a new short-acting GABAA receptor agonist developed by HengRui Medicine Co., Ltd., China. It has been approved by the National Medical Products Administration as a new anesthetic and sedative in 2019 [42]. Remimazolam tosylate has been investigated as a novel ultra-short-acting benzodiazepine in a phase III clinical trial for procedural sedation in China [43]. The study showed that a single dose of remimazolam tosylate (5.0 mg), followed by top-up doses as necessary, was noninferior to propofol in providing adequate sedation, with a very high success rate for patients undergoing upper gastrointestinal endoscopy. The initial low dose of 5.0 mg for remimazolam tosylate may not sufficiently induce rapid sedation. Thus, investigations on the optimized initial loading dose remain to be warranted.

Based on previous studies [44–46], we administered fixed doses of sufentanil. Fixed-dose administration is convenient and more in line with clinical practice.

Based on the existing data, remimazolam tosylate is promising to be used as a sedative agent for outpatient procedural sedation where predictable and rapid recovery is highly desirable. However, no clear standard has been established for the current dosage. Excessive use can cause respiratory depression, a fatal condition when involving personnel without professional training in airway management. Furthermore, if the dosage is insufficient, the participant cannot achieve ideal sedation. Further studies on human subjects are needed to completely characterize its action, which will define the optimal dosing regimens and to determine whether metabolite accumulation with prolonged infusion delays recovery.

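### The adverse-event form includes an item that only capnography can detect and grades apnea by duration, but the stated monitoring has no capnography and the respiratory record has no apnea field

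*Protocol article*

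**What the plan says.** All of the following is in the protocol article.

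- **Monitoring.** Besides SpO2, the Procedure of the trial says that "heart rate, continuous right upper limb noninvasive blood pressure, and Modified Observer’s Assessment of Alertness/Sedation (MOAA/S) score will be monitored". Table 2 repeats the list as "SpO_2_, heart rate, blood pressure, MOAA/S score". Readings are taken at set moments and, during the examination, "After successfully inserting the upper gastrointestinal endoscope, every 3 min until the end of upper gastrointestinal endoscopy".
- **Respiratory record.** Table 3 holds SpO2 before the procedure, "Lowest SpO_2_ during the procedure", whether SpO2 fell below 90% and for how long, and four airway interventions (more oxygen, jaw lift, mask ventilation, intubation).
- **Adverse-event form.** Step 2 of Table 4 lists subclinical respiratory depression as a Minimal descriptor. Footnote a describes it as "defined as capnographic abnormalities suggesting respiratory depression that do not manifest clinically". Non-prolonged apnea is a Minor descriptor, and the Sentinel column has "Apnea, prolonged (>60 s"). Staff tick whatever applies, and Step 5 takes the severity from the worst box ticked.
- **Use of the form.** Outcome measures adopts the tool for all adverse events during the procedure, and Additional analyses uses it for coding and promises counts and percentages. The Statistical analysis plan section compares adverse-event incidence by chi-square.

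**The concern.** An event can be counted only if the trial has a way of seeing it. Subclinical respiratory depression is, by its definition, a capnographic finding without clinical signs, and footnote a is the only place where the article mentions capnography. The form has no option for an item that was not assessed, so an empty box means either that the event did not happen or that nobody could have known.

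Apnea raises a related but weaker problem. It can be seen at the bedside, but the form needs its duration as well, and no field or procedure captures that. Because Step 5 grades by the worst box, a pause longer than 60 s that nobody timed could be entered as Minor instead of Sentinel, or not entered.

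What is at stake is the respiratory part of the safety table. Readers would see a percentage for an event that was never measured. They would also see an apnea comparison whose completeness depends on how closely staff happened to watch. Allocation masking describes only participants as blinded, and Adverse event reporting and harm says that drug-related events are collected nonsystematically.

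**Working it through.** The plan states no figure on this point, so there is nothing to reproduce. The check sets each respiratory item on the form against what is monitored or recorded.

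| Item on the adverse-event form | What is needed to record it | Is that in the monitoring text, Table 2 or Table 3? |
|---|---|---|
| Desaturation, minor or Sentinel | SpO2 and its duration | Yes: SpO2 monitored; lowest value and time below 90% recorded |
| Subclinical respiratory depression | Capnography, by definition | No |
| Apnea, not prolonged | Breathing observed and timed | No field; clinical observation is not excluded |
| Apnea, prolonged | Breathing observed and timed against 60 s | No field; clinical observation is not excluded |

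**Counts.** Step 2 of Table 4 has seven Minimal and four Sentinel descriptors. One of the seven cannot be measured with the listed monitoring. Two apnea descriptors, one of the four Sentinel ones among them, have no stated timing.

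**The capnographic item.** The recorded rate is the true rate times the probability of detection. Without capnography that probability is 0 by definition, so the recorded rate is 0% in every arm whatever the true rate. If a table showed 0 of 600, a reader applying the rule of three would infer an upper 95% bound of 3/600 = 0.5%, when the trial holds no information on the rate. This only illustrates how such a row would be read. The protocol does not commit to printing it. Removing the item from the count of participants with any event would change nothing, since it adds nobody to that count.

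**Do the scheduled readings help with apnea?** After insertion they are 3 min = 180 s apart. If a 60 s pause starts at a random moment in that gap, the chance that a reading falls within it is 60/180 = 1/3, and a single reading would still not give its length. A respiratory rate added at the Table 2 times would therefore not settle the grading. A field tied to the event would.

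**What incomplete recording of apnea could cost.** The documents give neither an apnea rate nor a detection probability, so the following rests on assumptions: true rates of 10% and 5%, 600 per arm, a two-sided 0.05 test, and the same detection probability *s* in both arms. Recorded rates are p1 = 0.10*s* and p2 = 0.05*s*, with mean p. Power is Φ{[(p1 − p2) − 1.96·√(2p(1 − p)/600)] / √([p1(1 − p1) + p2(1 − p2)]/600)}.

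| *s* | Recorded rates | Power |
|---|---|---|
| 1 | 10% vs 5% | 91% |
| 0.5 | 5% vs 2.5% | 63% |
| 0.25 | 2.5% vs 1.25% | 36% |
| 0.1 | 1% vs 0.5% | 17% |

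For *s* = 0.5: (0.025 − 1.96 × 0.01097)/0.01095 = 0.32, and Φ(0.32) is about 0.63. If *s* differed between arms, the comparison would be biased as well as weakened.

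**The case against.** The strongest reply is that this is a standard reporting tool taken over whole. Many of its items, such as seizure, airway obstruction and hypersalivation, have no scheduled measurement either, and are recorded when someone sees them. That is how adverse events are normally captured, and apnea fits the pattern. The article also condenses a fuller protocol that may say how breathing is watched. The capnographic item belongs to the lowest risk class, which footnote m describes as posing no danger of lasting harm on its own. Finally, the named respiratory secondary outcome, hypoxia, is defined by SpO2 and has its own fields.

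Most of this stands for apnea: nothing printed excludes bedside observation, so the defect is the missing duration and the uneven chance of recording. It does not rescue the capnographic item. Nobody can notice at the bedside an event defined as having no clinical sign, and both the monitoring list and the form are printed and do not match.

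A reader might go further in four ways that the documents do not support.

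- **That apnea, too, will be falsely recorded as absent.** This follows by definition only for the capnographic item.
- **That respiratory depression is the trial's main hazard.** The Discussion does warn that "Excessive use can cause respiratory depression, a fatal condition when involving personnel without professional training in airway management", but the Abstract names cardiac and pulmonary events together as the primary concerns.
- **That the trial sets out to show less respiratory depression than with propofol.** The aims are general. Where the Background and Discussion cite an adverse-effect advantage over propofol, they name injection pain and hypotension.
- **That routine oxygen makes SpO2 uninformative.** The protocol says of all participants: "They will be administered supplemental oxygen (3–4 L/min) before injecting sufentanil until the participants are fully alert after the procedure". That this delays desaturation is a reasonable inference, but the article does not state it, and SpO2-based events are still measured.

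**Conclusion.** The point holds as an inconsistency between Table 4 and Tables 2 and 3. For subclinical respiratory depression it is certain on the monitoring as printed: the recorded rate is 0% in all arms and carries no information. For apnea it is a risk of under-recording or uneven recording, of unknown size; the power figures above show only how much incomplete recording could matter under assumed rates.

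The primary outcome, SpO2-defined hypoxia and the desaturation items are unaffected. So is the sample size. The conclusion assumes that Table 2 is the complete list of monitored variables, as its title suggests. If some or all centres use capnography, the article should say so, and the item's denominator should be limited to participants monitored that way. The correction is worth making because it is cheap and decides what the safety table can be read to show.

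**What to change.** Reconcile Table 4 with Tables 2 and 3 in two steps.

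1. Add to Table 3, identically in all arms, whether apnea was observed (yes or no) and how long it lasted, in parallel with the existing field for time with SpO2 below 90%. Take the Minor or Sentinel grade of apnea from that duration.
2. Report subclinical respiratory depression as *not assessed*, not as 0%, wherever capnography is not used, and say so in a footnote to the safety table.

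The cost is one or two case report form fields, a footnote and slightly more recording for the sedation team. Timing a pause also needs someone to be watching when it occurs. Observed apnea remains less sensitive than capnography, so the safety report should state that apnea was ascertained by observation.
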